### Sample size calculation

2.11

The sample size was determined based on the primary outcome. The team conservatively anticipated a medium effect size for the group difference (Cohen's *f* ≈ 0.175, which corresponds roughly to d ∼0.35–0.40 in pairwise terms) given prior results based on the prior study on healthy individuals (11). Power analysis (*α* = 0.05 two-tailed, 1 − *β* = 0.80) for a one-way analysis of covariance (ANCOVA) with 4 groups and baseline as covariate, assuming the covariate explains ∼20% of variance, indicated needing about N ≈ 105 participants per group to detect *f* = 0.175. Allowing for up to ∼35% dropout, due to the fully online nature and 8-week duration, we decided to increase the target enrollment to ensure at least 105 completers per arm. Including the two extra groups for the conditioning test, the total planned sample size is *N* = 630 (105 × 6). This large sample will provide adequate power not only for primary comparison but also to explore secondary endpoints. Interim analyses are not planned; all data will be analyzed after study completion. The qualitative data from open-ended questions will be analyzed using deductive-inductive qualitative content analysis to identify patterns and themes in participants' experiences. We will integrate quantitative and qualitative findings in interpretation to understand the intervention's impact under consideration of multiple perspectives.

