## Introduction

1

Adults with subsyndromal generalized anxiety often experience significant distress and impairment comparable to those with clinical generalized anxiety disorder (GAD) (1). Despite this burden, these individuals may not qualify for standard treatments and thus benefit from accessible, preventive interventions. Self-help techniques like relaxation training, mindfulness, or hypnosis delivered digitally offer promising avenues for supporting this group. In particular, hypnosis and hypnotherapy have demonstrated effectiveness in reducing anxiety and stress. Reviews find that hypnotherapy can significantly lower anxiety levels and simultaneously modulate the autonomic nervous system by reducing sympathetic arousal and increasing parasympathetic tone (2). This physiological shift under hypnosis is associated with relaxation and could potentially be cardioprotective (2).

Aromatherapy with essential oils is another complementary strategy shown to alleviate anxiety. For example, inhalation of lavender (*Lavandula angustifolia Mill.*) essential oil has repeatedly been found to reduce stress and anxiety and improve mood in various populations (3–5). Likewise, bergamot (*Citrus bergamia*) essential oil-rich in limonene, linalool, and linalyl acetate-has demonstrated calming, anxiolytic effects. Clinical studies report that bergamot oil aromatherapy can lower heart rate and blood pressure and reduce stress and anxiety levels (6–8). These essential oils are generally safe and well-tolerated, making them suitable for a wide application in anxiety relief settings (9). Importantly, lavender and bergamot have distinct aromatic profiles and chemical compositions, allowing researchers to compare their effects on relaxation. Both oils' anxiolytic properties, documented in the literature, provide a strong rationale for their use in a stress-reduction intervention.

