### Data analysis

2.13

The primary outcome (MDBF calmness subscale change from T0 to T1) will be analyzed using an ANCOVA model. The model will include the study group (4 arms for primary analysis: Groups 1–4) as the independent variable and the baseline MDBF score as a covariate to control for any initial differences and improve statistical power. This aligns with the principle of analyzing covariance to account for baseline variance. The primary contrast of interest is whether either of the two combination groups (1: Hypnosis + Bergamot, 2: Hypnosis + Lavender) differ significantly from the control groups (3: Hypnosis-only, 4: Minimal intervention) in adjusted mean relaxation at T1. We anticipate a significant overall group effect; planned pairwise comparisons with appropriate correction for multiple comparisons, if needed, will examine specific differences, especially 1 vs. 3, 2 vs. 3, and combined 1&2 vs. combined 3&4. The primary hypothesis will be supported if Groups 1 and 2 show statistically greater increases in relaxation than Group 3 and Group 4 (*p* < .05, two-tailed).

For Phase 2 conditioning effects, a similar ANCOVA or mixed-model approach will be used at T2. The analysis will focus on the four groups that underwent Phase 2 aroma testing (Groups 1, 2 with match vs. Groups 5, 6 with mismatch). We will compare relaxation outcomes at T2 among these, using T1 values as covariates. A significant difference (e.g., match > mismatch) on the MDBF relaxation change from T1 to T2 or on the Phase 2 VAS responses would support H2.1. We may also use repeated measurements ANOVA or multilevel modeling incorporating all three time points (T0, T1, T2) to examine group × time interactions across the full study duration. The VAS data from each session will be analyzed using linear mixed-effects models, which can handle multiple observations per participant. These models will test differences in immediate relaxation gain per session by group and can also model time trends (session number as a predictor) to see if there is a significant upward trend in pre-session relaxation over the 6 weeks for each group (learning effect).

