All secondary continuous outcomes (anxiety, stress, sleep, well-being, worry scores) will similarly be analyzed via ANCOVA at T1 and T2 controlling for baseline, comparing the four main groups. We expect trends favoring the combined intervention, but these will be interpreted with caution and adjusted for multiple comparisons since multiple scales are involved. Moderator analyses (H2.3) will be exploratory by including interaction terms in the ANCOVA or regression models or conduct subgroup analyses splitting the sample by median age. Given the sample size (∼105 per arm planned), the trial is powered primarily for the main effect on the primary outcome; subgroup effects would have to be large to be detectable, so these findings will be descriptive.

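### The sample-size section's 80% power is stated for a four-group ANCOVA and not for the rule that decides the primary hypothesis, and the printed 105 per group does not follow from that test

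*Protocol article*

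**What the plan says.** Section 2.11 (Sample size calculation) gives the error rates as "Power analysis (*α* = 0.05 two-tailed, 1 − *β* = 0.80". The test is described as "for a one-way analysis of covariance (ANCOVA) with 4 groups and baseline as covariate", "assuming the covariate explains ∼20% of variance", and the result is about 105 participants per group. The effect size is "Cohen's *f* ≈ 0.175, which corresponds roughly to d ∼0.35–0.40 in pairwise terms". The section concludes that the sample gives adequate power for the primary comparison.

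Section 2.13 (Data analysis) then states the decision rule: "The primary hypothesis will be supported if Groups 1 and 2 show statistically greater increases in relaxation than Group 3 and Group 4", at p < .05 two-tailed. The same section also words the primary contrast as whether either combination group differs from the controls. It lists 1 vs 3, 2 vs 3, and 1&2 vs 3&4 as planned comparisons, corrected for multiplicity if needed. It later says that "the trial is powered primarily for the main effect on the primary outcome".

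Section 2.10 (Hypotheses) has a directional primary hypothesis (Groups 1 and 2 against Group 3 or 4). Beside it stands a formal alternative that is purely omnibus: at least one group differs.

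**The concern.** Cohen's f for four groups describes how far the four means spread, and the ANCOVA group F test detects any spread. The rule in section 2.13 is directional and, read literally, joint: both combination arms above both controls. A trial can have ample power for the first and little for the second, because a large gap to the minimal control is enough to make the F test significant.

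The only bridge between the two is the conversion of f to a pairwise d, which names no pair. It matters most for the comparison with hypnosis-only, the one that isolates what the oil adds. The Introduction takes the view that "hypnosis and hypnotherapy have demonstrated effectiveness in reducing anxiety and stress". If hypnosis alone does move the outcome here, the same f leaves a smaller d against Group 3.

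A non-significant result for Group 1 or 2 against Group 3 would be read against a published 80%. It could then be reported as evidence that oil adds nothing, when the comparison had far less power than that.

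**Working it through.** **Inputs from section 2.11:** f = 0.175, two-sided α = 0.05, R² = 0.20, n = 105 per group. The outcome SD is set to 1. All 105 are taken as completers, which is favourable: the planned total is 105 × 6 = 630, and 35% loss from 105 would leave about 68.

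**Step 1: the plan's own figure.** For the omnibus F, λ = 4n·f²/(1 − R²), with 3 and 4n − 5 df.
- n = 105: λ = 420 × 0.030625 / 0.8 = 16.08, power 93.3%.
- n = 73: λ = 292 × 0.030625 / 0.8 = 11.18, power 80.5%; n = 72 gives just under 80%.
- Ignoring the covariate, 80% needs 90 per group, and 105 gives 86.3%.

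So 105 is not the answer to the test described. A single two-arm comparison at d = 0.35 with R² = 0.20 has noncentrality (0.35/√0.8) × √(105/2) = 2.835 and power 81%. It reaches 80% at 104 per arm by exact t (103 by normal approximation). That is what 105 matches.

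**Step 2: what f = 0.175 implies pairwise.** Let Groups 1 and 2 have equal means, with a = d against Group 3 and b = d against Group 4. The variance of the four means is [a² + b² − (a + b)²/4]/4 = 0.175², that is, 3a² + 3b² − 2ab = 0.49.
- a = 0.35 gives 3b² − 0.7b − 0.1225 = 0, whose positive root is b = (0.7 + 1.4)/6 = 0.35. Groups 3 and 4 are then equal.
- Hypnosis alone gives 25% of the combined effect (a = 0.75b): 3.1875b² = 0.49, so b = 0.392, a = 0.294.
- Hypnosis alone gives 50% (a = 0.5b): 2.75b² = 0.49, so b = 0.422, a = 0.211.
- Hypnosis alone gives all of it (a = 0): 3b² = 0.49, so b = 0.404.

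Thus d = 0.35 against Group 3 needs equal means in Groups 3 and 4. When hypnosis alone works fully, d of about 0.40 arises against Group 4 only.

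**Step 3: power of each reading of the rule.** Simulated adjusted means (400,000 runs, n = 105, R² = 0.20, pooled residual variance on 4n − 5 df), unadjusted two-sided 0.05, counted in the favourable direction. The hypnosis-alone share is my assumption.

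| Criterion | Share 0 | Share 25% | Share 50% |
|---|---|---|---|
| Omnibus F | 93% | 93% | 93% |
| 1 vs 3 alone | 81% | 66% | 40% |
| Each of 1 and 2 beats each of 3 and 4 | 54% | 46% | 23% |
| Pooled 1&2 beats 3 and beats 4 | 83% | 76% | 50% |
| At least one of 1, 2 beats both 3 and 4 | 85–86% | 79% | 56% |
| 1&2 vs 3&4 | 98% | 98% | 95% |

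A search over patterns of means at f = 0.175 found none that lifts the third row above about 54%. A Bonferroni correction over three comparisons would lower that row to 34% (share 0) and 11% (share 50%), and 1 vs 3 to 67% and roughly a quarter.

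**The case against.** **The f-to-d phrase is not wrong arithmetic.** It names no pair, and 0.35 to 0.40 does span two legitimate patterns: 1 = 2 > 3 = 4 (0.35) and 1 = 2 = 3 > 4 (0.404). This stands. A reader might infer that the quoted d holds only if hypnosis does nothing, but that is true only of the comparison with Group 3. What remains is that the range is printed without saying which comparison it applies to.

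**The low figures come from holding f fixed while varying an assumed share.** Partly right. The document gives no share, and the Introduction's statement about hypnosis is general literature, not an effect on this outcome against this control. Fix d = 0.35 against Group 3 instead, with hypnosis giving half the effect. Then 1 vs 3 stays at 81%, the four-comparison rule reaches 70%, and the pooled rule about 90%. But those means (0.70, 0.70, 0.35, 0) imply f = 0.29 and d = 0.70 against Group 4, neither of which section 2.11 states. The four-comparison rule still falls short of 80%.

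**Other readings are well powered.** Also right in part. Section 2.9 calls combined groups against control conditions the key comparison, and 1&2 vs 3&4 has 95–98% power. It would be wrong to infer that no reading, or only one, reaches 80%. But that contrast averages the minimal control into the comparator. With f = 0.175 and oil adding nothing (1 = 2 = 3 > 4), it is still significant about 64% of the time, so it cannot show that oil adds to hypnosis.

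**The formal hypotheses in section 2.10 are omnibus and match section 2.11.** They match in form, but section 2.13 states when the hypothesis counts as supported.

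**Details of multiplicity belong in an analysis plan.** Accepted. The conclusion rests on the uncorrected figures.

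**Conclusion.** The point holds in this form. Section 2.11 attaches 80% power and 105 per group to a test that needs 73 per group and has 93% power at 105. The rule in section 2.13 has no stated power. Read arm by arm, it has at most about 54% at f = 0.175, falling to 23% if hypnosis alone gives half the combined effect. The oil-versus-hypnosis-only comparison has about 80% power only in the pattern where Groups 3 and 4 have equal means.

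These figures assume 105 completers per arm, R² = 0.20, equal effects of the two oils, no multiplicity correction, and f fixed at 0.175. The 0–50% share is an illustrative range, not a figure from the document.

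A reader might infer that the 80% is correct for the omnibus test and merely misapplied, or that the trial must enrol more. Neither is supported. The omnibus figure is itself not 80%, and whether the sample suffices depends on which criterion the authors mean. Sections 2.10 and 2.13 leave that open between any difference, either combination group, and both.

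**What to change.** In section 2.13, name one deciding success criterion, and bring the omnibus alternative in section 2.10 and the either-group and both-groups wordings in section 2.13 into line with it.

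In section 2.11:
- State the assumed d separately for combination versus hypnosis-only and combination versus minimal control, in place of the general f-to-d equivalence.
- Replace the 80% with the power of the named criterion at the planned number per arm, including any multiplicity correction.
- If an omnibus figure is kept, correct it to about 93% at 105 completers per arm, and say that it does not apply to the oil-versus-hypnosis-only comparison.

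Adjust the sentence in section 2.13 about what the trial is powered for to match.

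The cost is a short calculation and rewording in sections 2.10, 2.11 and 2.13. Conduct and enrolment do not change. The downside is that the stated power will probably be less favourable.

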**Methods:**

This study protocol describes a randomized controlled trial evaluating the efficacy and conditioning potential of a digital self-hypnosis intervention combined with essential oil inhalation in adults with subsyndromal generalized anxiety. A total of *N* = 630 participants will be randomized into six groups. Four groups enter the primary efficacy analysis: (1) self-hypnosis + bergamot essential oil, (2) self-hypnosis + lavender essential oil, (3) self-hypnosis without essential oil, and (4) a minimal-intervention control. The intervention is delivered online over six weeks (Phase 1), followed by a two-week conditioning phase without hypnosis (Phase 2), in which stimulus-specific effects of the essential oils are tested. The primary outcome is subjective relaxation, measured by the Multidimensional Mood Questionnaire (MDBF) at baseline, post-intervention (6 weeks), and post-conditioning (8 weeks). Secondary outcomes include anxiety symptoms, perceived stress, sleep quality, well-being, and worry. In a voluntary subsample, heart rate variability (HRV) and pulse wave variability (PWV) will be assessed as physiological correlates of relaxation. In addition, the questionnaires are expanded to include open-ended questions, enabling an exploratory assessment of participants’ experiences, attitudes, and reflections on the intervention and its potential for sustainability. This approach complements quantitative results with qualitative insights and may reveal new perspectives for future research.

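### Section 2.11 promises at least 105 completers per arm after up to 35% dropout, but randomizes only 105 per arm, and the 105 does not follow from the stated power inputs

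*Protocol article*

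**What the plan says.** Section 2.11 (Sample size calculation) describes a power analysis "for a one-way analysis of covariance (ANCOVA) with 4 groups and baseline as covariate", with alpha 0.05 two-tailed and 80% power, "assuming the covariate explains ∼20% of variance". It reports that this "indicated needing about N ≈ 105 participants per group to detect *f* = 0.175" and adds that the effect size is one "which corresponds roughly to d ∼0.35–0.40 in pairwise terms".

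It then turns to attrition: "Allowing for up to ∼35% dropout, due to the fully online nature and 8-week duration", followed by "we decided to increase the target enrollment to ensure at least 105 completers per arm". The next sentence sets the total at 630, written as 105 × 6.

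Two other places fix what 630 means. The Methods paragraph of the abstract says that "630 participants will be randomized into six groups", and section 2.13 (Data analysis) again gives about 105 per arm as the planned size. Section 2.6 gives equal allocation to the six arms.

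**The concern.** If 105 per group are needed, and enrolment was raised so that 105 remain after dropout, the number enrolled per arm must exceed 105. It equals 105. The required number, the promised number of completers and the number randomized are all the same figure, so the stated increase does not appear in the total.

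The enrolment target decides when recruitment stops. A team following this text could close at 630 believing that 105 completers per arm were secured. The power claim is also the yardstick for reading a non-significant result. Section 2.13 ties support for the primary hypothesis to Groups 1 and 2 exceeding Group 3 and Group 4, and names 1 vs 3 and 2 vs 3 among the planned comparisons, so pairwise power matters alongside the omnibus test.

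**Working it through.** **Inputs, all from section 2.11:** f = 0.175; pairwise d about 0.35 to 0.40; alpha = 0.05 two-tailed; power 0.80; k = 4 groups; baseline covariate with R² = 0.20; dropout up to 0.35; 105 per group; 630 in total. The power figures assume a complete-case analysis, in line with the section's own reference to completers.

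**1. Can the 105 be reproduced?** Noncentral F with λ = N f² / (1 − R²), df1 = k − 1, df2 = N − k − 1.

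- As described (k = 4, R² = 0.20), at 73 per group: N = 292, λ = 292 × 0.030625 / 0.80 = 11.18, power 0.805. At 72 per group power is 0.799. The need is therefore 73 per group, not 105.
- Ignoring the covariate gain (R² = 0): 90 per group.
- At 105 per group with R² = 0.20: N = 420, λ = 16.08, power 0.933, well above the stated 0.80.
- A two-group comparison at d = 0.35 (f = d/2 = 0.175) with R² = 0.20 needs 104 per group. This comes close to 105, but it is not the test that the section names.

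**2. Completers.**

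- 105 × 0.65 = 68.25 per arm, so 68.
- 630 × 0.65 = 409.5, about 410 in total.
- To keep 105 completers: 105 / 0.65 = 161.5, so 162 per arm; 162 × 6 = 972.

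**3. Power at 68 completers per arm (R² = 0.20, no multiplicity adjustment).**

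| Test | Effect | λ | Power |
|---|---|---|---|
| 4-group F-test, N = 272 | f = 0.175 | 272 × 0.030625 / 0.80 = 10.41 | 77% |
| Pairwise, 68 vs 68 | d = 0.35 | 136 × 0.030625 / 0.80 = 5.21 | 62% |
| Pairwise, 68 vs 68 | d = 0.40 | 136 × 0.04 / 0.80 = 6.80 | 74% |
| Pooled 1&2 vs 3&4, 136 vs 136 | d = 0.35 | 272 × 0.030625 / 0.80 = 10.41 | about 90% |

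The pairwise effect detectable with 80% power is about d = 0.43 at 68 per arm, against about d = 0.35 at 105 per arm.

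**4. Break-even for the omnibus test.** 80% power returns at 73 completers per arm, which corresponds to dropout of 1 − 73/105 = 30%.

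**The case against.** The strongest reply is that little is lost on the only test for which section 2.11 states a power. On the plan's own inputs that test needs 73 per group, so 105 randomized tolerates about 30% dropout, and at 35% power is still 77%. This stands.

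The 35% is also an upper bound, tied to the 8-week duration, whereas the primary endpoint is at week 6. Loss by T1 cannot exceed loss over the 8 weeks and may be smaller. So 68 per arm is a worst case, not an expectation.

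The pairwise figures rest on choices that the article does not fix. It states no pairwise power and only a range for d. Section 2.13 leaves the multiplicity correction open, so no particular adjusted power can be charged to the plan. The pooled contrast, which section 2.13 also names, remains well powered.

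A reader might infer that 105 was really derived from a two-group comparison. The near match at 104 does not establish that, because 73 / 0.70 = 104.3 also rounds up to 105 and would make it an already inflated figure. The documents give neither derivation. The second possibility does not rescue the text either: section 2.11 presents 105 as both the number needed and the number of completers, and inflating 73 for 35% dropout gives 73 / 0.65 = 112.3, so 113 per arm.

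None of these replies removes the conflict between the promised completers and the number randomized.

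**Conclusion.** Section 2.11 is wrong as written in two respects. First, 630 randomized cannot ensure 105 completers per arm at the stated dropout; as few as 68 would remain. Second, 105 per group is not the answer to the 4-group calculation described, which gives 73.

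The consequence for power depends on the test. At worst-case dropout it is under 3 percentage points for the omnibus F-test. It is material for 1 vs 3 and 2 vs 3, at 62% to 74% over the plan's own range of d before any adjustment. The pooled contrast is little affected. These figures assume R² = 0.20, complete-case analysis and the full 35% loss by T1.

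A reader might go further and conclude that the primary analysis as a whole is seriously underpowered, or that 630 leaves no margin for dropout under any calculation. The documents do not support either: by the described 4-group calculation, 105 per arm carries a margin of about 30%.

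**What to change.** Rewrite section 2.11 so that its figures agree:

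- State 630 randomized, 105 per arm, and as few as 68 completers per arm (about 410 in total) at 35% dropout.
- Give the resulting power with its assumptions: 77% for the 4-group F-test at f = 0.175 and R² = 0.20; 62% at d = 0.35 and 74% at d = 0.40 for a single unadjusted pairwise comparison, with about d = 0.43 detectable at 80% power; about 90% for the pooled contrast at d = 0.35.
- Remove the promise of at least 105 completers per arm. If the sponsor prefers to keep it, the target must become 162 per arm, 972 in total, and the abstract and section 2.13 must follow.
- Correct the 105, or state the calculation that actually produced it. Only the authors can supply this; no derivation should be inserted by inference.

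Keeping 630 costs a change of wording, with a matching registry update if the same statement appears there, and a less favourable power statement. Keeping the promise costs 972 − 630 = 342 more participants.

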### Biosignal processing

2.12

A total of 15 min of ECG (130 Hz) and photoplethysmographic (PPG; 28 Hz) data will be collected from all participants of the sub-study during the resting conditions at T0 and T1. The ECG data will be recorded using a Polar H10 chest-strap, and the PPG data will be recorded using a Polar Verity Sense optical pulse sensor. The participants will remain in a seated position during the recording. The time series estimating functions of the autonomic regulation will be semi-automatically extracted from the raw data using Kubios HRV Scientific Software for the ECG and an in-house software (programming environment Matlab R2025a) for the PPG, derived as follows:
time series of heart rate, consisting of successive beat-to-beat intervals [BBI, (ms)],time series containing maximum PPG peak amplitudes per heartbeat [PPGMAX, (a.u.)], andtime series containing minimum PPG peak amplitudes per heartbeat [PPGMIN, (a.u.)].Afterwards each 15-min time series will be filtered by applying an adaptive variance estimation algorithm to remove and interpolate ectopic beats and artefacts to ensure normal-to-normal time series (NN) (21). Afterwards indices describing autonomic regulation will be calculated in the time domain (TD), in the geometric domain [Baevsky's stress index (22)], the frequency domain (FD) (the power spectra of equidistant linear interpolated NN interval time series will be obtained by applying the Fast Fourier Transformation), and in the nonlinear domain (NLD) (Table 1).

**Table 1 T1:** Definition of clinically relevant HRV indices and their assignment to the autonomic nervous system.

Domain	Index	Unit	Definition and explanation	Activity as part of the autonomic nervous system
Time domain	meanNN	ms	Mean value of all NN intervals	—
	SDNN	ms	Standard deviation of NN intervals in the measurement time range	Sympathetic nervous system and parasympathetic nervous system
	SDANN	ms	Standard deviation of the average of NN intervals in 5-min segments	Sympathetic nervous system and parasympathetic nervous system
	RMSSD	ms	“Root Mean Square of successive differences” (Square root of the mean value of the sum of all squared differences between adjacent NN intervals)	Parasympathetic nervous system
	NN50	beats	Number of pairs of adjacent NN intervals that differ by more than 50 ms	Parasympathetic nervous system
	pNN50	%	Percentage of consecutive NN intervals that differ by more than 50 ms	Parasympathetic nervous system
Geometric	SI		Stress Index, square root of Baevsky stress index, reflects cardiovascular stress	Sympathetic nervous system
Frequency domain	TP	ms^2^	Total Power: Total power or total spectrum; corresponds to energy density in the spectrum from 0.00001 to 0.4 Hz (VLF, LF and HF)	No clear assignment
	VLF	ms^2^	“Very low frequency power” (Power density spectrum in the frequency range of 0.003–0.04 Hz)	Parasympathetic nervous system
	LF	ms^2^	“Low frequency power” (Power density spectrum in the frequency range of 0.04–0.15 Hz); LFn [n.u.]	Sympathetic and parasympathetic nervous systems, with the parasympathetic nervous system predominating
	HF	ms^2^	“High frequency power” (Power density spectrum in the frequency range of 0.15–0.40 Hz); HFn [n.u.]	Parasympathetic nervous system
	LF/HF	—	Ratio of LF and HF	Sympathetic-parasympathetic balance
Nonlinear dynamics Poincaré-Plot	SD1	ms	Standard deviation of the point distances to the transverse diameter	Parasympathetic nervous system
	SD2	ms	Standard deviation of the point distances to the longitudinal diameter	Sympathetic nervous system and parasympathetic nervous system

In NLD most prominent measures will be applied describing important features such as nonlinearity, time irreversibility, fractality, and long-range correlations of physiological dynamics. As one example described in more detail, Symbolic dynamics (SD). The idea of SD is based on simplifying the non-linear dynamics (the way things change over time) that are part of time series (23). Consequently, the NN will be transformed into a symbol sequence of four symbols with a given alphabet *A* = {0, 1, 2, 3}. The creation of words from this new alphabet (consisting of a symbol string) will be achieved through the utilization of three successive symbols, thereby enabling 64 distinct word-type combinations (bins) (000, 001,…,333). The following SD indices from the probability distribution of each word-type within the symbol sequence will be estimated:
wpsum02: Relative portion (sum/total) of words consisting only of the symbols “0” and “2”, a measure for reduced variability [a.u.], andwpsum13: Relative portion (sum/total) of words consisting only of the symbols “1” and “3”, a measure for increased variability [a.u.].Further NLD HRV which will be applied are Poincaré plot analysis (PPA) (24), Approximate (ApEn) and Sample entropy (SampEn) (25), Multiscale entropy (MSE) (26) and Detrended fluctuation analysis (DFA) (27) (Table 1). Although TD and FDmethods facilitate the quantification of HRV on disparate time scales, NLD methods furnish supplementary information with regard to the dynamics and structure of beat-to-beat time series. Notwithstanding, the disadvantage associated with these methodologies partly remains the complexity involved in the physiological interpretation of the results (23, 28).

